### Standard cardiac rehabilitation care

All participants will be offered the standard outpatient CR program provided by each hospital, which involves education classes and supervised exercise.

### Study intervention

In addition to standard CR care, the mHealth intervention group will receive the core components of CR delivered via text messages (also known as *short messaging service* (SMS)) and a supporting website over the course of 24 weeks. The intervention will be delivered primarily by SMS because SMS is readily available to all mobile telephone users, inexpensive and easy to use. Participants will be offered brief training in how to use SMS and the Internet if necessary. Each intervention participant will receive a NZ$20 telephone credit voucher to reimburse any costs associated with replying to intervention messages. No changes will be made to the intervention or study design once recruitment begins; however, participants can choose to stop receiving the intervention and will be informed of this option during the consent process. A SMS library of 503 messages has been developed. It is written in English at an appropriate reading level (RMS 800 Lexile: approximately age 13 years) tested using the Lexile Analyzer 2013 software program (MetaMetrics, Durham, NC, USA). Intervention participants will receive five to seven messages per week for 24 weeks.

The overall goals of the intervention are to have individuals adhere to clinician-prescribed New Zealand CHD treatment
[8] and American College of Sports Medicine guidelines
[28]. Intervention content is based on the current CR guidelines, previous trials
[19,29,30] and developmental studies. Content will be delivered on two aspects of self-management to improve participants’ condition and manage the emotional distress often associated with CHD: illness perceptions and lifestyle changes.

### Illness perceptions

Messages will address illness perceptions and medication-related beliefs using the Common-Sense Model
[31]. The intervention will focus on modifying people’s perceptions of treatment for secondary prevention of CHD with regard to symptoms, timelines, causes, consequences, understanding of CHD treatment, personal control over CHD treatment and the effectiveness of CHD treatment. A lower perceived threat of illness has been shown to predict CR attendance and return to work in MI patients
[32]. Messages will contain information and strategies to help participants stick to their prescribed medication regimen, information on the value of taking medication in terms of reducing subsequent events and hospitalisation, and reminders to have a regular checkup with their physicians.

### Lifestyle changes

The intervention includes education and support to eat a healthy diet, manage stress, exercise regularly, reduce alcohol consumption and stop smoking (if needed). Additional SMS will be delivered based on the suboptimal behaviour participants most wish to modify (outlined below), which will be identified at the baseline assessment.

#### Physical activity

Content was adapted from the HEART trial, and messages will be sent regarding the importance of being physically active, suggested activities and key strategies (for example, goal-setting and self-monitoring) to enhance uptake and maintenance of physical activity. General exercise prescription will be offered, detailing the type, frequency, duration and intensity of exercise based on participants’ preferred activities
[28]. A pedometer will be provided to participants in the intervention group to assist with self-monitoring of daily activity.

#### Heart healthy diet

Participants will be supported to eat a heart-healthy diet and manage their weight. This support will include large servings of fruits and vegetables, whole grains, lean meats and alternatives while limiting intake of saturated fat, salt, alcohol and sugar
[8]. Participants will receive text messages promoting healthy eating strategies, overcoming barriers and advice on choosing healthy food and food preparation.

#### Stress management

Participants will receive education to improve their quality of life through the identification and treatment of psychological distress. Treatment includes learning relaxation techniques and specific coping strategies to be used during times of stress, as well as avoiding harmful behaviours (that is, alcohol consumption). Strategies will be emphasised that facilitate participants’ return to a full and active life by enabling the development of their own resources. A health psychologist has aided in the development of these messages.

#### Stopping smoking

Participants who smoke tobacco will receive components of successful cessation interventions by text messaging
[33] and video messaging
[29]. They will be sent regular messages providing smoking cessation advice and support (for example, symptoms to expect upon quitting, tips to avoid weight gain during and after cessation and to cope with craving, and advice on avoiding smoking triggers).

The lifestyle change component is framed by social cognitive theory (SCT)
[34]. A key construct of SCT is self-efficacy, or the confidence to engage in a desired behaviour, which has been shown to be a mediator of behaviour change
[35] and is an outcome of CR
[36]. Specific behaviour change techniques (BCTs)
[37] that have been reported to be effective in changing health behaviours in a CHD population
[38,39] will be used to target the constructs of SCT. All text messages are coded according to their SCT construct and related BCTs (see Additional file
2 for a sample).

### Supporting website

A secondary component of the intervention is a secure supporting website (Text4Heart homepage,
https://text4heart.co.nz/, which is archived by WebCite at
http://www.webcitation.org/6KNUFTSwm; see Additional file
3 for screenshots). A number of interactive features have been created to increase interactivity and website usage
[30]. The website includes a blog whereby participants can ask questions and receive answers and social support, as well as a graph with which participants can monitor their physical activity by texting their pedometer counts, which will then be automatically uploaded. Additional information will be provided regarding CR, taking medications, various forms of physical activity, healthy eating, smoking cessation and hyperlinks to other websites (for example local exercise programs and cardiac clubs).

Efficacious beliefs can be enhanced through the use of vicarious learning, or *role modelling*, which refers to the process of learning behaviours by viewing other people’s behaviours and the outcomes of those behaviours
[36]. Role modelling will be incorporated into the intervention through the use of short videotape messages (30 to 60 seconds) on the participant website. The video clips will involve a variety of CHD patients discussing their experiences of lifestyle change, the types of problems they faced, how they coped and any advice they can offer. Brief vignettes outlining the benefits of CR and healthy lifestyles, physiological responses, and safety issues will be provided by exercise scientists, nutritionists and cardiologists. Participants will receive occasional text messages (approximately once per fortnight) prompting them to view the website.

### Tailoring

A recent mHealth review found that personalised interventions were more effective at changing behaviour; however, few study researchers had implemented tailored components
[17]. The Text4Heart intervention is personalised according to each participant’s name, choice of suboptimal behaviour and the time of day messages are sent. Bidirectional messages are included that require the participant to respond, such as texting in pedometer step counts, which then trigger a tailored response from the study team. Participants will be able to ‘text an expert’ to request personalised feedback, with questions answered by the researchers within 48 hours. This dynamic feedback loop holds promise to improve health behaviour, as rapid two-way communication provides participants with just-in-time information or strategies
[40]. The intervention is designed to be automated and thus minimize human involvement; however, participants will be encouraged to connect with a real person (study team member) to ask questions if needed.

The corresponding author is responsible for monitoring the website and responding to incoming text messages from participants, as well as for updating the video page and blog with news and tips twice per week. The only planned personal contact from the study team will occur at 12 weeks after randomisation, when a member of the research team will telephone participants to remind them about the study, check on their progress against goals and answer any questions. Both the intervention and control groups will receive this telephone call to ensure that any between-group differences are the result of the text messages and the website, not human contact. The multifaceted approach of personalised SMS, videotape messages, website usage and opportunities for telephone contact may better encourage disease self-management than a unifaceted, SMS-only intervention
[41].

### Primary outcome

The primary outcome is adherence to recommended lifestyle behaviours, which will be measured using a composite health behaviour score adapted from the EPIC-Norfolk Prospective Population Study
[27]. In the present study, the measures described below will be used to determine participants’ health behaviour scores.

1. Smoking status will be measured using a common smoking history questionnaire
[42]. This eight-item questionnaire is used to assess smoking status (current smoker, ex-smoker or nonsmoker), the number of cigarettes smoked per day and history of quit attempts.

2. Physical activity level will be assessed using the Godin Leisure Time Physical Activity Questionnaire (GLTPAQ)
[43]. This simple three-item questionnaire has well-established reliability and validity and has been used in patients undergoing CR (*N* = 826)
[44].

3. Alcohol consumption will be measured using the Alcohol Use Disorders Identification Test alcohol consumption questions (AUDIT-C)
[45], a screening tool designed to assess units of alcohol consumed per week and to identify people who are hazardous drinkers. The AUDIT-C has been used as a primary care screening test for alcohol dependence in a sample of 243 older men with medical conditions, including heart disease
[45]. Index cards referencing standard drink sizes will be used to reduce comprehension errors.

4. Fruit and vegetable intake will be assessed by two New Zealand–specific questions used in the 2006/2007 New Zealand Health Survey (*N* = 12,488, including adults with CHD)
[46]. Index cards referencing standard fruit and vegetable serving sizes will be used to aid recall.

Participants will receive a score on a four-point scale, with one point each assigned for being a current nonsmoker, meeting physical activity guidelines to achieve some health benefits (14 units or more as scored on the GLTPAQ), consuming fourteen or fewer standard alcoholic drinks per week
[27] and consuming at least five servings of fruits and vegetables per typical day
[27].

### Secondary outcomes

The following are the secondary outcomes of the present study.

1. We will measure the difference in absolute CVD risk score
[47] at 6 months after randomisation. This measure was developed for predicting risk in people with previous CVD events, but has also been applied to secondary prevention populations as a composite measure of changes in risk factors. The individual risk factors that form the absolute CVD risk score include age, lipid levels, blood pressure, and smoking and diabetes status.

2. Body composition will be measured using body mass index and waist-to-hip ratio. Physical measurements will be taken as the average of two readings.

3. Illness perceptions will be assessed using the Brief Illness Perception Questionnaire (B-IPQ)
[48]. The B-IPQ has been used in a cardiac setting to examine speed of recovery following MI
[32]. Items are scored on scales from zero to ten and can be collapsed into smaller clusters of causal beliefs. When items are combined, a higher score represents a more threatening perception of the participant’s disease.

4. Self-reported medication adherence will be assessed using the Morisky 8-item Medication Adherence Scale (MMAS)
[49]. The MMAS has been used in a sample of patients with hypertension and has been found to predict reasons for poor adherence
[50]. It will be completed at the 6-month assessment, as at baseline participants may not yet have been discharged from hospital with their new medications. Items are answered as yes or no, and scores are combined to indicate low, medium and high medication adherence. A list of participants’ prescribed medications will also be collected.

5. Self-efficacy will be assessed using the Self-efficacy for Managing Chronic Disease 6-item Questionnaire
[51]. This six-item questionnaire has well-established reliability and validity on the basis of its use in a sample of participants with chronic disease, including heart disease (*N* = 1,130). Items are scored from one to ten, with a higher combined score indicating higher self-efficacy.

6. Mood will be assessed using the Hospital Anxiety and Depression Scale (HADS)
[52]. The HADS performed well in assessing anxiety disorders and depression in somatic, psychiatric and primary care patients as well as in the general population. Participants will be asked to choose one of four answers to each item (six items for depression and six for anxiety). Each answer is assigned a score and added up to determine the indicated normal to abnormal levels of anxiety and/or depression.

7. Engagement in the intervention (for example, number of messages read, visits to the study website and number of contacts with the study team) will be assessed in exit surveys and on the basis of website usage statistics gathered by a website visit tracking system.

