### Study sample and recruitment

Eligible participants are English-speaking New Zealand adults (ages 18 years and older) with a documented diagnosis of CHD (myocardial infarction (MI), angina or revascularisation) who meet the criteria for usual CR care and have access to the Internet (for example, library, work or home access). A basic mobile telephone with which to receive text messages will be available on loan to participants who do not own one (fewer than one in ten New Zealanders). Exclusion criteria are untreated ventricular tachycardia, severe heart failure, life-threatening coexisting disease with life expectancy less than 1 year, and/or significant exercise limitations for reasons other than CHD.

Potential participants will be screened during hospital admission at two metropolitan hospitals in Auckland, New Zealand. The annual incidence of hospitalisation for CHD in New Zealand overall is approximately 162 people per 100,000
[26] and over 2,400 in the Auckland area. The recruitment strategy was effective in the HEART trial
[20,21]. Potential participants will receive a study information sheet while in hospital, and informed consent will be obtained from participants at the baseline assessment. All patients will be offered usual CR care. Assessments will be conducted in hospital, community clinics or participants’ homes to encourage retention.

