### Outcome assessments

Assessments will be conducted at baseline and 6 months postrandomisation (see Figure 
1). Baseline assessments will involve an explanation of study procedures, signed consent and collection of demographic details. Participant-reported primary and secondary outcomes will then be collected, followed by physical measurements, including height, weight, waist and hip circumference, blood pressure and blood cholesterol. The baseline assessment concludes with randomisation and assignment of participants to the respective study groups.

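### For text-message engagement, item 7 of the secondary outcomes names only an exit survey that could apply, although the two-way messaging system and the study team handle usable data on every intervention participant

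*Protocol article*

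**What the plan says.** The protocol article, Secondary outcomes, item 7, defines the outcome as "Engagement in the intervention (for example, number of messages read, visits to the study website and number of contacts with the study team"). It then gives the sources: engagement "will be assessed in exit surveys and on the basis of website usage statistics gathered by a website visit tracking system".

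Other sections bear on how well those sources fit:

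- **Study intervention** makes SMS the main channel and sets the dose: "Intervention participants will receive five to seven messages per week for 24 weeks". **Supporting website** describes the website as the secondary component.
- **Tailoring** describes an automated, two-way system: "Bidirectional messages are included that require the participant to respond, such as texting in pedometer step counts". Replies trigger a tailored response, and participants can text questions that the researchers answer within 48 hours. **Supporting website** adds that texted step counts are uploaded automatically to a graph.
- **Study intervention** allows early stopping: "participants can choose to stop receiving the intervention and will be informed of this option during the consent process".
- **Outcome assessments** fixes the time points: "Assessments will be conducted at baseline and 6 months postrandomisation". **Study sample and recruitment** adds: "Assessments will be conducted in hospital, community clinics or participants’ homes to encourage retention".
- **Statistical analyses** applies intention to treat and makes all secondary analyses exploratory.

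**The concern.** The sources are matched to the components the wrong way round. The secondary component is measured automatically, while the main one depends on self-report. Self-report has two weaknesses here. Respondents must recall about half a year of messages, and anyone lost before the 6-month assessment gives no answer, although that person's messaging history would still exist in a system record.

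The stake is interpretation. Item 7 is the only place where the article plans to measure how much of the intervention was taken up, and for SMS it leans on the weaker source. If the primary result were null, an overstated SMS uptake would favour the reading that participants were engaged and the content did not work, over the reading that many received or used little of it. The Discussion itself stresses the need to learn which parts of such an intervention work.

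**Working it through.** **Step 1. Match each engagement measure to a source.** The document states no figure for engagement, drop-out or survey response, so there is no figure to reproduce. The first check is a comparison of sections.

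| Measure | Named source that could apply (item 7) | Other data described elsewhere |
|---|---|---|
| Website visits | Automatic tracking | – |
| Messages read | Exit survey only | None; a system log cannot show reading |
| Contacts with the study team | Exit survey; item 7 does not say it is the only one | The team answers the texts itself (Tailoring) |
| Replies, step-count texts, expert queries | Not listed as measures | Handled by the system or team (Tailoring, Supporting website) |
| Stop requests | Not listed | Must be acted on for sending to cease (Study intervention) |

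The article does not say what the system stores or can export. That such records exist is an inference from how the system is described.

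**Step 2. The recall task.** The planned dose is 5 × 24 = 120 to 7 × 24 = 168 messages, with midpoint (120 + 168)/2 = 144. A respondent would have to say how many of these were read.

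**Step 3. Effect of missing surveys.** Let m be the share of intervention participants without an exit survey, c the fraction of messages read by respondents, and r the reading of the missing relative to respondents.

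- Mean reported by the survey: c
- Mean over all participants: (1 − m)c + m·r·c
- Overstatement: c − [(1 − m)c + m·r·c] = m × c × (1 − r)

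The document gives none of m, c or r. The values below are assumptions: c = 0.80, with messages counted out of 144.

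| m (of 60) | r = 0.75 | r = 0.50 | r = 0.25 |
|---|---|---|---|
| 0% (0) | 0 | 0 | 0 |
| 10% (6) | 2 points (2.9 messages) | 4 points (5.8) | 6 points (8.6) |
| 20% (12) | 4 points (5.8) | 8 points (11.5) | 12 points (17.3) |
| 30% (18) | 6 points (8.6) | 12 points (17.3) | 18 points (25.9) |

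Worked cell: m = 0.20, r = 0.25 gives 0.20 × 0.80 × 0.75 = 0.12, and 0.12 × 144 = 17.3 messages. With r = 1 the result is zero for any m.

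The formula covers non-response only. Recall error among respondents comes on top, and the document gives nothing from which to size it.

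**The case against.** A reader might infer more: that the survey misses everyone who stops early, so that the reported dose will be that of completers and is bound to be too high. The document does not support this. The option it describes is that "participants can choose to stop receiving the intervention", which is not the same as leaving the trial. With intention to treat, a 6-month assessment and home visits on offer, someone who stops the texts can still be surveyed, and nothing restricts the survey to those who finish 24 weeks. Upward bias needs both missing surveys and lower engagement among the missing.

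Three further objections carry weight.

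- **A log does not measure reading.** A participant who ignores every text but never asks to stop would appear fully dosed if messages sent were taken as messages read. That stands, and it limits what the log may be used for. The log still gives stop dates and replies, which do not depend on attending an assessment.
- **The article is a condensed document.** Who is surveyed, when, and with what denominator may well be set out elsewhere, and their absence is not a fault. Item 7 does state its sources, however, and the wording that marks the list as examples attaches to the measures and not to the sources.
- **The outcome is exploratory.** That is correct, and it caps the importance of the point.

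**Conclusion.** The point holds in a limited form. For text-message engagement, item 7 names a source that depends on long recall and on reaching participants at 6 months, while the described system and team handle more objective data on the same component. Overstated uptake is plausible but not established. It rests on the assumption that those lost before the assessment engaged less, and its size cannot be derived from the document; the 2 to 18 points shown are illustrations under assumed values. The primary comparison, its power and its error rate are untouched. This is a cheap improvement to one exploratory secondary outcome.

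**What to change.** In Secondary outcomes, item 7:

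1. Take SMS engagement from messaging-system and team records: messages sent before any stop request, date of the stop request, replies to bidirectional messages, step-count texts, expert queries and contacts with the team.
2. Report these with all randomised intervention participants (planned 60) as the denominator.
3. Seek the exit survey from all of them, including those who have stopped the messages. Report self-reported reading as a respondents-only supplement, with the number responding.
4. State that messages sent are not to be reported as messages read.

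The cost is a short addition to the text and a data export, provided the system keeps the records; that should be confirmed first. The change alters neither the intervention nor the trial design, so it is compatible with the commitment in Study intervention to change neither once recruitment begins. The remaining drawback is that logs show sending and replying, so reading will still rest on self-report.
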